## Methods

### Overall design

The intervention mixed methods design involves a stepped-wedge cluster randomized controlled trial testing the outcomes of training in recovery-oriented practice, together with an embedded qualitative study to identify the contextual enablers and challenges to implementing recovery-oriented practice within primary care settings. Eighteen general practices and community health centers were randomly allocated to one of two steps (9 months apart) to start an intervention comprising general practitioner training in the delivery of recovery-oriented practice. Data collection consists of cross-sectional surveys collected from patients of participating general practitioners at three time points: baseline, and again at the end of Steps 1 and 2 (see Fig. 1). A mixed methods design was chosen for a number of reasons, including that it would produce richer and more complete findings than that based on either the qualitative or quantitative approach alone. Combining these approaches can further explain and enhance the integrity of the project outcomes, so that a mixed methods design may assist with project credibility, particularly when multiple stakeholders are involved such as in the PULSAR project [28]. The use of qualitative and quantitative methods were integrated at different stages of the intervention trial [27]. Initially, qualitative methods were used in an exploratory manner to identify potential barriers to recovery-oriented training within primary care settings, and to inform the intervention design. Subsequently, quantitative methods are being used to then measure the effectiveness of the intervention. Following the intervention trial, qualitative methods will be used in an explanatory manner to gain a more nuanced understanding of GP experiences of implementing recovery-oriented practices and patient experiences of these practices [28]. Quantitative and qualitative data are collected from patient participants, but only qualitative data are collected from GP participants.

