### PALS: PULSAR active learning sessions

GPs and other professionals who have received the PULSAR training are invited to participate in monthly one-hour online sessions called “PALS (PULSAR Active Learning Sessions)” with consultant specialist psychiatrists to review, reflect and share their experiences in the implementation of recovery-oriented practice. These sessions provide an interactive learning environment for supporting practice-based implementation of learning from the PULSAR resources and training package.

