#### Sample size targets

The study has two sample groups: GPs and patients of these GPs. Sample size calculations were done using Stata statistical software *stepped-wedge*: for clusters defined at the level of the general practice site, the primary outcome measure is the QPR, with a published mean of 46 and standard deviation of 16, power of 0.80, significance level set at 0.05, intraclass correlation coefficient (ICC) within practice sites of 0.05, the number of steps (2), and patient data collected cross-sectionally at three time points (baseline, Step 1, and Step 2).

The original sample target was a minimum of 20 different sites (clusters) with one GP per site; each GP was required to recruit a minimum of 30 patients during the four-year project (10 patients at baseline, 10 at Step 1, and 10 at Step 2), resulting in a minimum of 600 patient participants overall.

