### Procedures to minimize bias

The study GPs could not be blinded to the intervention allocation as the intervention involved GP training. Therefore, the following procedures to minimize other sources of bias have been adopted:Wherever possible, the research assistants, administration staff, and data entry staff are blinded to the intervention allocation.Patients enrolled: procedures undertaken to minimize contamination include that participating patients are not advised by the research team if their GPs has received the intervention training.Control clusters: patients in the control clusters continue to receive treatment as usual. As the study has a stepped-wedge design, all sites will receive the intervention by Step 2. Stepped-wedge designs are often preferred for such community-based pragmatic trials as they can minimize contamination of control clusters as staff and clinicians in all sites know that the study intervention is eventually coming [32–34].Recruitment: capacity to give informed consent is presumed for the majority of people and provisions are made to ensure those most in need are given the opportunity to participate. For example, the recruitment sampling method outlined above allows for maximum numbers of patients to be identified who then have a choice in deciding whether or not they would like to participate in research. This is done to assist in avoiding possible sampling bias and gives flexibility for patients to respond based on possible fluctuations in mental health. Ethics research indicates that people with serious mental illness are able to provide informed consent to participate in research, especially if particular efforts are made to recruit them [50]. Research also indicates that, for people with mental health issues, participating in research can lead to positive reactions such as a sense of enjoyment and empowerment, and is beneficial for improved service delivery [51, 52]. It is presumed that those who do not wish to participate, or those who are unable to understand the study goals and procedures, will not return the consent forms and completed measures.Allocation: all randomization was carried out by the statistician in the research team following the appropriate procedures set out earlier.In analysis: wherever possible, the data collectors and data entry team are blinded to allocation status and do not have access to information about the allocation of clusters. Study data are entered into a study database that does not contain information about intervention status.

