### Main analysis plan

Descriptive statistics will be used to summarize the characteristics of the patient-level variables and the GP clinics (clusters), see Table 2. Cluster-level variables are those used in the stratified randomization, which are four types of organizational variations, plus the intervention status of the cluster and the time since (or before) the intervention. The intraclass correlation coefficient (ICC) will be calculated and reported.

**Table 2 Tab2:** Individual and cluster-level variables available for multivariable analysis

Variable	Description
*Individual level*	
Demographics	
Sex	Sex of patient.
Age	Age of patient at survey completion date.
Country of birth	Country of birth of patient.
Ethnicity	Ethnic or cultural group that the patient identifies with.
Main language	Main language spoken at home.
Marital Status	Marital status of patient.
Living situation	Current living situation of patient.
Education	Education level of the patient.
Health Economics	
Mental health medications	Medications for mental health taken regularly by the patient.
Employment	Current working status of the patient.
Income	Usual weekly income of patient, after tax, from all sources of employment.
Days out of role	Number of days in the past month that the patient was totally or partly unable to carry out normal activities because of mental health problems.
Days absent from work	Number of days in the past month that the patient was absent from work due to illness or disability, and due to mental health problems.
Hospitalizations	Number of hospital admissions for physical problems and for mental health problems, including number of nights in total and reasons for most recent admissions.
Consultations with health professionals	Number and length of consultations with health professionals for physical health and mental health problems.
GUPI	The General-Practice Users’ Perceived-need Inventory is a one-page instrument developed to assess participants’ estimation of their needs for mental health care and the meeting of those needs.
*Cluster level*	
Cluster group	Allocated to receive the intervention at either Step 1 or Step 2.
Intervention status (0/1)	A lag time of six months is anticipated until intervention effects are possible. The intervention status variable indicates that this lag time has passed.
Dosage (%)	Intervention dosage.

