Time since intervention	All patient surveys are time-stamped in relation to the time the intervention was received at the cluster. Time value of “0” is given for the plus/minus three months from date of training; “1” for four-to-six months post training; “2” for seven-to-nine months post training, etc. Time value of “-1” for four-to-six months before training; “-2” for seven-to-nine months before training, etc.
Time	Study month that survey was completed: “0” = December 2014, “1” = January 2015, etc.
*Cluster level stratification variables*	
Clinic type	Privately owned general practice vs community health center.
GP clinic size	GP equivalent full time (EFT) size greater than 5 (yes/no).
Clinic location	Local government area location: Dandenong, Casey, Cardinia, other.
Specialist focus clinic	A specialist focus clinic (yes/no) was determined by more than 10% of the practice patients belonging to any of the following groups: a. people with HIV/AIDS b. people with enduring and serious mental illness (e.g., schizophrenia, bipolar disorder) c. people with permanent physical disabilities d. people with addictions e. homeless people f. transient/seasonal populations g. people living in poverty h. Aboriginal peoples i. recent immigrants (six months or less) j. people from cultural minorities k. people with sports injuries l. other

The primary analysis will examine the patient-level QPR scores (continuous data) at baseline, nine months (Step 1), and 18 months (Step 2), using a linear mixed-effects model. The model will include intervention status and time as fixed effects and clusters and patients as random effects. Both univariate and multivariable models will be developed based on baseline patient and cluster-level variables considered statistically significant (*p <* 0.10) or clinically important (e.g., age, sex), see Table 2, and included in the model as fixed. This will include the intervention dosage variable described earlier. Model fit will be examined by comparing AIC values.

Secondary analyses will examine the patient-level data of the INSPIRE, WEMWBS, and K10. Similar to the primary analysis, we will use linear mixed-effects models to compare the intervention and control periods (pre-intervention) for continuous outcomes and generalized linear mixed-effects models for binary outcomes.

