Estimated intervention effects will be reported as the mean outcome difference for continuous outcomes and Odds Ratio for binary outcomes between intervention and control periods, assuming a constant treatment effect over time. This can be described as a meta-analysis approach as (in the case of continuous data) the mean change in each cluster will be standardized by using the variance of the outcome measure within that cluster. The estimated intervention effects will be reported with 95% Confidence Intervals and *p* values. Analysis will be conducted using Stata V.14, StataCorp. Stata Statistical Software: Release 14. College Station, TX: StataCorp LP, 2015.

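### With every practice trained by the last survey, the constant-effect estimate puts a negative weight on the longer-term effect, so it is not the average effect if the effect changes after training

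*Protocol article*

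**What the plan says.** All references are to the protocol article.

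- **Model** (Main analysis plan): "The model will include intervention status and time as fixed effects and clusters and patients as random effects". Intervention status is a 0/1 variable. Table 2 defines time as "Study month that survey was completed" and does not say whether it enters as categories or as a linear trend.
- **Reported effect** (Main analysis plan): the mean difference "between intervention and control periods, assuming a constant treatment effect over time".
- **Design** (Overall design; Procedures to minimize bias): 18 clusters, two steps and three cross-sectional surveys, and "all sites will receive the intervention by Step 2".
- **Lag** (Table 2): "A lag time of six months is anticipated until intervention effects are possible". The same entry adds that the status variable marks when this lag is over.
- **After training**: GPs "are invited to participate in monthly one-hour online sessions" (PALS section). The Dosage section tracks whether trained GPs stay in the cluster.
- **Sensitivity analyses**: the only one described is multiple imputation for missing data.

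**The concern.** Early clusters are surveyed in two periods after training, late clusters in only one. At the last survey no cluster is untreated. Under a constant effect the two groups should then not differ because of treatment, and the model uses their difference at that survey only to correct for underlying cluster differences. If the second-period effect differs from the first, part of that difference is treatment effect, and the model subtracts it.

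What is at stake is the meaning of the headline QPR result. A reader would take a single effect under this heading as a sensible average over the post-training time studied. If the effect changes with time since training, it is not one, and it can lie outside the range of the two true effects.

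**Working it through.** **Inputs from the protocol.** SD 16, ICC 0.05, two steps, three surveys, 10 patients per GP per survey (Sample size targets); 18 clusters (Overall design); 30 GPs (Adaptations to GP recruitment and retention). This gives 10 patients per cluster-period with one GP per cluster, and 10 × 30/18 = 16.7 on average with all 30 GPs.

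**Assumed.** Clusters split 9 and 9, equal cluster-period sizes, exchangeable within-cluster correlation, training on schedule, and status equal to 1 for all surveys in a post-training period.

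**The plan's own figure.** 20 clusters × 30 patients = 600 is correct. No target difference is stated, so the power cannot be reproduced. Under the model below, 600 patients give 80% power for 6.93 QPR points (0.43 SD).

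**Weights, time categorical.** Let D₁, D₂, D₃ be early minus late cluster means at the three surveys. The treatment patterns are (0,1,1) and (0,0,1), so

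E[D₁] = 0, E[D₂] = d1, E[D₃] = d2 − d1.

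The generalised least squares estimate of a constant effect is D₂ − w(D₁ + D₃), with w = τ²/(σ²/m + 2τ²). Its expectation is

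(1 + w)·d1 − w·d2.

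With total variance 256, τ² = 0.05 × 256 = 12.8 and σ² = 243.2:

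- m = 10: w = 12.8/(24.32 + 25.6) = 0.256
- m = 16.7: w = 12.8/(14.59 + 25.6) = 0.318

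**Other codings of time.**

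| Time | d2 weight, m = 10 | d2 weight, m = 16.7 |
|---|---|---|
| Categorical | −0.256 | −0.318 |
| Linear, equal spacing | −0.256 | −0.318 |
| Linear, study months 2, 8, 11 | −0.071 | −0.119 |

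Months 2, 8 and 11 are the February, August and November 2015 midpoints under Statistical analyses. With m = 20 that last row gives −0.135. At ICC 0 the weight is zero with categorical or equally spaced time and slightly positive (+0.13) with linear time at those midpoints.

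**Consequences (categorical time).**

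| True pattern | Estimate/d1, m = 10 | Estimate/d1, m = 16.7 | Average/d1 |
|---|---|---|---|
| d2 = 2·d1 | 1.256 − 0.512 = 0.74 | 1.318 − 0.636 = 0.68 | 1.5 |
| d2 = d1 | 1.00 | 1.00 | 1.0 |
| d2 = 0 | 1.26 | 1.32 | 0.5 |

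The expected estimate reaches zero when d2/d1 = (1 + w)/w, which is 4.9 (m = 10) or 4.1 (m = 16.7). With linear time at the stated midpoints, doubling gives 1.071 − 0.142 = 0.93 (m = 10) or 1.119 − 0.238 = 0.88 (m = 16.7).

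**Precision (18 clusters, m = 16.7, categorical time).** The SE of the constant effect is 2.07 QPR points. With separate terms it is 2.18 for d1, 3.54 for d2 and 2.73 for (d1 + d2)/2. In that model D₃ is used up in estimating d2, so d1 rests on baseline and Step 1 alone.

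**The case against.** - **The lag is already handled.** This stands. The six-month lag is built into the status variable, so a reader who takes it as evidence that the effect varies once status is 1 goes further than the text. It does not remove the problem, because after the switch the model still assumes one effect for early and late clusters.
- **The protocol never says the effect grows or fades.** This also stands. The monthly sessions are optional, and nothing states that they strengthen the effect. They and possible loss of trained GPs are only reasons why a constant effect cannot be taken for granted.
- **Dosage and time since intervention are available covariates.** Dosage may absorb part of any fading caused by loss of trained GPs. It does not separate first- from second-period effects. Time since intervention, in three-month bins, is only listed as available, and its coding in a model is not fixed. The reported effect remains a constant one.
- **The size depends on idealisations.** This stands in part. Training delays are expected, the coding of time is open, and linear time at the stated midpoints makes the weight much smaller.
- **A constant effect is a conventional, openly stated choice.** True, and it is why the constant-effect model can stay. The problem is what its estimate can be taken to mean in this design.

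A reader might infer that training which works better over time would be reported as harmful, or would readily give a null result. The figures do not support that: an expected null needs a second-period effect 4 to 5 times the first under categorical time, and more under linear time at the stated midpoints.

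**Conclusion.** The concern holds as a conditional one. At the planned ICC the constant-effect estimate gives the second-period effect a negative weight: −0.26 to −0.32 with categorical or equally spaced time, and about −0.07 to −0.13 with linear time at the stated midpoints. If the effect is the same in both periods there is no bias. If it differs, the estimate lies outside the range of the two true effects, below both under growth and above both under fading.

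The result rests on the ICC of 0.05, an equal split of clusters, equal cluster-period sizes and training on schedule. A cluster autocorrelation of 0.8 still gives −0.22 to −0.27 with categorical time. The documents do not establish that the effect will change, only that the plan has no prespecified analysis that would show it. The change should be made, because the data are already being collected and it limits what a constant-effect result can be taken to show.

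**What to change.** State whether time is categorical or linear. Beside the constant-effect model, prespecify a model with separate terms for the first and second post-training periods. Report d1, d2 and (d1 + d2)/2 with 95% confidence intervals, and state in advance that the constant-effect estimate will not be interpreted as the average effect if d1 and d2 differ.

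No new data are needed. The cost is precision: against 2.07 for the constant effect, the SE rises by about 5% for d1 (2.18), 32% for the average (2.73) and 71% for d2 (3.54). With so few clusters, a non-significant difference between d1 and d2 is weak evidence that the effect is constant, so the intervals should be read, not only a test. Replacing the headline estimate by d1 alone is not recommended without discussion: with categorical time it draws nothing from the Step 2 survey, and it gives the longer-term effect no weight.

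### The Main analysis plan describes the reported effect in a way that conflicts with its own mixed model; followed literally, that description would absorb any calendar trend in the outcome

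*Protocol article*

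**What the plan says.** All the statements at issue stand close together in the protocol article, Main analysis plan.

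- The primary model is a linear mixed-effects model for patient-level QPR: "The model will include intervention status and time as fixed effects and clusters and patients as random effects".
- The reported quantity is then named: "Estimated intervention effects will be reported as the mean outcome difference for continuous outcomes and Odds Ratio for binary outcomes", a contrast "between intervention and control periods, assuming a constant treatment effect over time".
- The next sentence says this can be described as a meta-analysis approach because, for continuous data, "the mean change in each cluster will be standardized by using the variance of the outcome measure within that cluster".

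The design sections matter for what the last statement implies. Overall design: "Eighteen general practices and community health centers were randomly allocated to one of two steps (9 months apart" months), and "Data collection consists of cross-sectional surveys collected from patients of participating general practitioners at three time points". Procedures to minimize bias: "As the study has a stepped-wedge design, all sites will receive the intervention by Step 2".

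**The concern.** The first two statements fit together: the natural reading is the intervention-status coefficient of a model that adjusts for time, expressed in QPR points. The third does not fit. A mean change per cluster, standardised with that cluster's own variance and then pooled, has no time term and weights clusters differently. If standardising means dividing, it is also no longer in QPR points.

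In this design the missing time term matters. Crossover runs one way, so each cluster's intervention data are always later than its control data. A within-cluster change therefore mixes the training effect with whatever else moved QPR over the period. It also leaves out the comparison that randomisation provides, namely trained against not-yet-trained clusters at Step 1. Because the surveys are cross-sectional, the change is between different patients as well.

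At stake is the primary estimate with its confidence interval and p value. Two analysts following the same section could report different primary results, and the wording leaves room to choose between them after the data are seen.

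**Working it through.** **Inputs from the article**
- 18 clusters, two steps (Overall design).
- SD 16, ICC 0.05, 10 patients per GP per period, significance level 0.05, taken as two-sided (Sample size targets).
- Exposure pattern over baseline, Step 1, Step 2, read from Table 3: 0,1,1 for the first sequence and 0,0,1 for the second.
- Timing. The primary analysis paragraph gives baseline, 9 and 18 months. Statistical analyses centres the collection windows on February, August and November 2015, that is 0, 6 and 9 months. Data collection and management gives months 4–6, 16–18 and 28–30, a 12-month spacing.

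**Assumed input.** A linear drift in QPR of b points per 9 months. The article gives no figure, so b = 0, 1 and 2 are illustrations.

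**1. Expected within-cluster change with no training effect**

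*9-month spacing*, period means 0, b, 2b:
- Sequence 1: (b + 2b)/2 − 0 = 1.5b
- Sequence 2: 2b − (0 + b)/2 = 1.5b

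The bias is equal in both sequences, so averaging over clusters cannot remove it.

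*February/August/November windows*, period means 0, (6/9)b = 0.67b, b:
- Sequence 1: (0.67b + b)/2 − 0 = 0.83b
- Sequence 2: b − (0 + 0.67b)/2 = 0.67b
- Average over equal sequences: 0.75b

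*12-month spacing* would give 1.5 × (12/9)b = 2.0b. The range below uses the first two schedules.

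**2. Standard error of the average change**

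Within-cluster variance = 256 × 0.95 = 243.2. Each cluster has one period of 10 on one side of the crossover and two periods (20) on the other:

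SE = √[243.2 × (1/10 + 1/20) / 18] = √2.027 = 1.42.

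**3. False-positive rate**

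P = Φ(bias/SE − 1.96) + Φ(−bias/SE − 1.96).

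| b per 9 months | Bias, stated windows | Rate | Bias, 9-month spacing | Rate |
|---|---|---|---|---|
| 0 | 0 | 5% | 0 | 5% |
| 1 | 0.75 | 8% | 1.5 | 18% |
| 2 | 1.5 | 18% | 3.0 | 56% |

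**4. Simulation check** (1000 trials per scenario, 18 clusters × 10 per period, 9-month spacing). The time-adjusted estimate treats period as categorical, with variances taken as known; the pooled change uses inverse-variance weights estimated from each cluster.

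| b | True effect | Time-adjusted estimate | Rejects | Pooled change | Rejects |
|---|---|---|---|---|---|
| 0 | 0 | 0.03 | 4.5% | 0.07 | 7.5% |
| 1 | 0 | 0.17 | 5.1% | 1.60 | 23.3% |
| 2 | 0 | −0.10 | 4.8% | 2.99 | 57.5% |
| 2 | 5 | 5.02 | 49.6% | 7.94 | 100% |

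The pooled change rejects somewhat more often than step 3 predicts, already at b = 0; estimating each cluster's weight from few patients would do this. Both estimators are unbiased when b = 0.

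**5. Scale, if standardising means dividing**

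A 5-point effect is 5/10 = 0.50 in a cluster with SD 10 and 5/22 = 0.23 in one with SD 22 (illustrative SDs). Divided by the variance itself, 5/256 = 0.02 per QPR point, which is not unit-free. A cluster SD from 30 patients has a relative sampling error of about 1/√(2 × 29) = 13%.

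**The case against.** The strongest reply is that the disputed sentence is a gloss. The section has already fixed a model with a time term and named a mean difference; only then does it offer a comparison with meta-analysis. It specifies no separate pooling step, formula or second model. That stands. A reader might infer that the trial will report secular drift as a training effect, but the article does not support this: if the reported figure is the model coefficient, time is adjusted for and the sentence merely misdescribes it.

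A second reply is that standardising by using the variance may mean inverse-variance weighting. This also stands as a possible reading. It would keep QPR points and remove the scale objection, but it would not add a time adjustment, so the conflict with the model remains.

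A third reply concerns the figures. The drift is assumed, and with none there is no bias. The 1.5b depends on 9-month spacing, and the stated windows halve it. Thirty patients per cluster also assumes one GP per site. With 30 GPs (Adaptations to GP recruitment and retention) at 30 patients each over 18 clusters, the target is 30 × 30/18 = 50 per cluster. The SD error is then 1/√(2 × 49) = 10%. The SE falls to √[243.2 × (1/16.67 + 1/33.33)/18] = 1.10, which raises the false-positive rates for the same drift. The rates are therefore conditional illustrations and not predictions.

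What the reply does not remove is that the sentence states how the change will be handled, and that this is not the coefficient of the specified model.

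**Conclusion.** The Main analysis plan contains two incompatible descriptions of the reported effect for continuous outcomes. The mixed model and the mean difference agree with each other; the sentence on cluster-wise standardisation agrees with neither. Followed literally, it would yield an unadjusted before-after estimate that takes in any calendar trend and leaves the randomised Step 1 contrast unused.

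The numerical consequence is conditional on two things: that this estimator and not the model coefficient is reported, and that QPR drifts over calendar time. Under a linear drift of b points per 9 months, the bias is about 0.75b to 1.5b depending on which of the article's schedules applies. With 18 clusters of 10 per period, the false-positive rate is then 5% at b = 0, about 8% to 18% at b = 1 and about 18% to 56% at b = 2. The primary model as specified is not affected, and neither is the sample size.

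**What to change.** Delete the meta-analysis sentence. In its place, state that the reported effect for continuous outcomes is the time-adjusted intervention-status coefficient from the linear mixed model of the Main analysis plan, in points of the scale concerned, with its 95% CI and p value. If a standardised effect is wanted, define it as supplementary: that same coefficient divided by one common pooled SD, not by each cluster's own.

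This settles the contradiction whichever way time is coded in the model; that coding is a separate choice and need not be reopened here. The cost is wording only, with no change to data collection, sample size or the primary model.
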